## Abstract

**Background:**

Adolescent idiopathic scoliosis (AIS) is a three-dimensional spinal deformity that progresses with age, making effective early intervention crucial to avoid surgical treatment. Traditional Chinese Medicine (TCM) Manual therapy (MT) offers the advantage of relaxing muscles and correcting biomechanical imbalances, thereby assisting patients in performing postural correction exercises under proper biomechanical alignment. However, evidence supporting the use of TCMMT for AIS remains limited.

**Objective:**

This study aims to elucidate the biomechanical changes in AIS patients by comparing with healthy individuals, and investigate the clinical efficacy and biomechanical mechanisms of combining TCMMT with Schroth method in the treatment of AIS.

**Methods:**

This study is a randomized controlled trial. Sixty eligible AIS patients will be randomly allocated in a 1:1 ratio to either the experimental group (EG) or the control group. All patients will undergo Schroth method for 60 min, five times per week. The EG will additionally receive TCMMT for 20 min, three times per week. The treatment course will be 8 weeks. Furthermore, fifteen age-matched healthy volunteers will be included. The primary outcome measure is the Cobb angle assessed before and after treatment. Secondary outcome measures include plantar pressure and 3D gait parameters, surface electromyography and muscular temperature. Adverse events will be recorded throughout the trial. All patients randomly allocated in this study will be included in the intention-to-treat analysis.

**Conclusion:**

This study will provide multi-dimensional evidence for the efficacy of TCMMT as an adjunctive treatment for AIS, advance the development of manual therapy within the field of rehabilitation, and facilitate its application in clinical decision which making by both physicians and patients.

**Study protocol registration:**

http://itmctr.ccebtcm.org.cn, identifier ITMCTR2025002392.

## Introduction

1

Scoliosis is defined as a lateral curvature of the spine greater than 10 degrees, accompanied by vertebral rotation, with Adolescent Idiopathic Scoliosis (AIS) being the most prevalent type (1). The incidence of AIS is approximately 2 to 4% and shows a consistently increasing trend (2, 3). While AIS can progress during growth and cause cosmetic issues, it is usually asymptomatic and easily overlooked. This neglect can lead to the progression of spinal deformity and overall biomechanical imbalance, resulting in decreased trunk stability and abnormal gait (4–6), which seriously jeopardizes the physical and mental health of adolescents. Therefore, seeking safe and effective early treatment options is of significant importance.

The Society on Scoliosis Orthopedic and Rehabilitation Treatment Recommends Physiotherapeutic Scoliosis-Specific Exercises (PSSE) as an important intervention to halt or slow curve progression (1). The Schroth method is one of the most common PSSE interventions. This method aims to achieve a three-dimensional correction of the patient’s specific curve pattern in daily life by integrating sensorimotor, postural, and corrective breathing exercises (7–9). The Schroth method has been shown to improve posture, alleviate pain, strengthen core muscles, and may contribute to slowing curve progression and reducing the need for surgery. However, the Schroth method requires patients to perform corrective postures under proper biomechanical alignment, but many patients cannot achieve or maintain the postures due to muscle imbalances and joint stiffness. Therefore, its efficacy is highly dependent on patient compliance and varies considerably among individuals (10–13).

According to Traditional Chinese Medicine (TCM) theory, musculoskeletal imbalance is a key etiological factor in AIS (14). As a TCM therapy, TCM manual therapy (MT) is regarded as a safe and effective therapeutic approach and widely used in the treatment of AIS (15–17). By reducing pain, decreasing spinal stiffness, and restoring biomechanical dysfunction in affected segments, TCMMT may enhance patients’ comfort and compliance with daily exercise. In addition, TCMMT allows patients to perform the effective Schroth method under corrected biomechanical alignment, which complements the benefits of exercise therapy (16, 18).

The lower limbs, pelvis and spine are interconnected. Existing studies have widely reported that AIS patients typically exhibit biomechanical abnormalities in both the spine and lower limbs, such as asymmetric muscle activation, temperature differences in muscle activity, gait abnormalities and abnormal plantar pressure distribution, which further compromise spinal stability by disrupting the biomechanical balance between spine and lower limbs (6, 19–21). Understanding these biomechanical features is important for developing personalized rehabilitation strategies for AIS. However, the biomechanical changes of AIS patients are still controversial (22–24). The impact of TCMMT on biomechanics also has not been fully elucidated, and the quality of relevant studies still needs improvement (25, 26).

Thermography is a useful and noninvasive method of assessing muscular tension imbalance in the course of scoliosis (27). Combining with the plantar pressure, 3D gait analysis, and surface electromyography (sEMG) enables a comprehensive evaluation of the spine-limb biomechanical patterns during standing and walking in patients. Consequently, this study will employ the Cobb angle, the gold standard for scoliosis assessment (28), and integrate plantar pressure measurements, 3D gait analysis, surface electromyography (sEMG) and infrared thermography (IRT) to evaluate biomechanical changes. The study aims to elucidate the characteristics of biomechanical changes in AIS during standing and walking by comparing with healthy individuals at baseline, and provide evidence-based support for the efficacy and safety of combined TCMMT and Schroth method therapy by comparing baseline and post-treatment data of AIS.

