#### Sample size consideration

2.2.6

According to previous research (31), the Cobb angle was 10.87 ± 3.60°in EG after treatment, compared to 14.97 ± 5.01°in CG. Using the PASS 2021 software for calculation, with a sample size ratio set at 1:1, *α* = 0.05 (two-sided test), and a statistical power (1−*β*) of 0.90, while controlling the attrition rate within 15%, it is determined that 30 patients need to be recruited for each group. Therefore, this study will require the inclusion of a total of 60 patients. In addition, we will recruit 15 healthy individuals of the same age. They will compare with patients at baseline to evaluate biomechanical changes of AIS.

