#### Data analysis

2.5.2

All statistical analysis will be performed by an independent statistician (blinded to group allocation) using SPSS 27.0. A *p*-value of <0.05 will be considered statistically significant. Continuous data will be summarized as mean ± standard deviation (M ± SD) or median with interquartile range. Categorical variables will be presented as frequencies or percentages.

This study will employ an intention-to-treat analysis, including all participants who were randomized and received at least one intervention session. Outcomes will be analyzed using two-sample *t*-tests or paired *t*-tests. If normality assumptions cannot be met, non-parametric tests will be used. For categorical variables, chi-square (χ^2^) tests will be performed. Inter-rater reliability will be assessed using the intraclass correlation coefficient. For case data with missing values, multiple imputation will be used to address the gaps.

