This study innovatively integrates plantar pressure measurement, 3D gait analysis, sEMG, and IRT to establish a multimodal quantitative assessment framework. This system comprehensively captures the biomechanical characteristics of AIS patients during both static standing and dynamic walking. The approach synergistically complements and validates findings across multiple dimensions, including postural support, movement patterns, muscle activation, and thermal asymmetry, thereby significantly enhancing the objectivity and accuracy of the observed metrics. This protocol will not only enable an in-depth exploration of the biomechanical mechanisms underlying postural and gait abnormalities in AIS patients but also provide a precise and individualized basis for evaluating the therapeutic effects of TCMMT. It will hold substantial value for clinical research and possess promising application prospects.

The study will be conducted in strict adherence to the protocol, and all researchers will receive unified, standardized training to ensure compliance with regulated trial procedures. Based on these rigorous methodological designs, we believe that the results of this trial will provide new evidence regarding the role of manual therapy in AIS and make a substantive contribution to the current evidence base for the physical therapy of scoliosis.

This trial shares similar limitations with previous studies. Due to the nature of the interventions, neither the physicians nor the patients could be blinded, which may introduce bias. However, the primary objective of this study is to evaluate the additive effect of TCMMT within the combined regimen, rather than to independently validate the effectiveness of exercise therapy. This study will focus on assessing the corrective effect of combining TCMMT with the Schroth method on biomechanical imbalance by integrating multiple quantitative and objective evaluation metrics.

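### The efficacy aim is worded as a before-after comparison and the analysis section does not say which t-test answers it, although the objective and the sample size call for EG versus CG

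*Protocol article*

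**What the plan says.** The last paragraph of the Introduction sets two aims. One is to characterise AIS against healthy volunteers at baseline. The other is to support efficacy and safety of the combined therapy, and the means given is "by comparing baseline and post-treatment data of AIS". The sentence names a comparator for the first aim and none for the second. Section 2.1 is similar: it speaks of observing patients before and after treatment. Section 2.4.1 has the Cobb angle measured before and after treatment and names no contrast.

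Section 2.5.2 states that outcomes will be analysed with "two-sample *t*-tests or paired *t*-tests", with non-parametric alternatives. No outcome, contrast or priority is attached to either test.

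Two other places point to the randomised comparison. The Discussion says that "the primary objective of this study is to evaluate the additive effect of TCMMT within the combined regimen". Section 2.2.6 plans on the statement that "the Cobb angle was 10.87 ± 3.60°in EG after treatment, compared to 14.97 ± 5.01°in CG". Section 2.3 gives both arms the same eight-week Schroth programme, with manual therapy added in EG only.

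**The concern.** The additive effect of manual therapy is identified only by the EG-CG contrast. A change from baseline within EG combines any effect of manual therapy with the effect of the Schroth exercises, growth over eight weeks and regression to the mean. A paired test in EG asks whether that sum is zero, which is not the question in the Discussion.

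The protocol itself makes a common improvement plausible, since the Discussion cites evidence that Schroth exercise reduces the Cobb angle. If the aim is followed as the Introduction words it, a significant EG change could be reported as evidence for the combined therapy when manual therapy contributed nothing. The same holds for plantar pressure, gait, sEMG and temperature, because section 2.5.2 applies one sentence to all outcomes.

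**Working it through.** **1. Which contrast does the sample size assume?**

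Inputs from section 2.2.6: "the Cobb angle was 10.87 ± 3.60°in EG after treatment, compared to 14.97 ± 5.01°in CG"; alpha "0.05 (two-sided test), and a statistical power" "of 0.90, while controlling the attrition rate within 15" per cent; "with a sample size ratio set at 1:1"; result: "it is determined that 30 patients need to be recruited for each group".

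- Difference: 14.97 − 10.87 = 4.10°.
- SD: √((3.60² + 5.01²)/2) = 4.36°. Standardised difference: 4.10/4.36 = 0.94.
- Normal approximation: n = 2(1.960 + 1.282)² / 0.94² = 23.8, so 24 per arm. 24/0.85 = 28.2, so 29 recruited.
- Noncentral t: 25 per arm gives power 0.902 (0.901 with unequal variances). 25/0.85 = 29.4, so 30 recruited.

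The stated 30 per group reproduces as a two-sample comparison of post-treatment Cobb angle. The trial was therefore sized for EG versus CG.

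**2. What does a paired test in EG show when manual therapy adds nothing?**

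Assume that both arms change equally and that 25 per arm are evaluable. With a standardised within-patient change d, the paired t statistic has noncentrality d√25 = 5d on 24 df.

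| Assumed common change d | Noncentrality | P(EG paired test significant) |
|---|---|---|
| 0.3 | 1.5 | 0.30 |
| 0.4 | 2.0 | 0.48 |
| 0.5 | 2.5 | 0.67 |
| 0.8 | 4.0 | 0.97 |

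In degrees, the SD of change is 4.36 × √(2(1 − r)), where r is the baseline-to-post correlation. The protocol gives no r and no expected change, so both are assumptions.

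| Common improvement | r = 0.5 (SD 4.36°) | r = 0.7 (SD 3.38°) | r = 0.9 (SD 1.95°) |
|---|---|---|---|
| 1° | 0.20 | 0.30 | 0.69 |
| 2° | 0.60 | 0.81 | 1.00 |
| 3° | 0.91 | 0.99 | 1.00 |
| 4.1° | 0.995 | 1.00 | 1.00 |

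In the same setting the two-sample t-test on change rejected in 4.9% to 5.1% of 20,000 simulated trials (improvements of 2° and 4.1°, r of 0.5 and 0.9), so it holds its nominal 5%.

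**3. What does a designated between-arm analysis cost in sample size?**

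Adjusting the post-treatment value for baseline reduces the residual SD to 4.36 × √(1 − r²). Power at 25 evaluable per arm for a 4.10° difference:

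- unadjusted post-treatment value: 0.902;
- adjusted, r = 0.5: 0.964;
- adjusted, r = 0.7: 0.995.

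No increase in N is needed.

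**The case against.** The strongest reply is that the plan already intends the between-arm test. The trial is randomised 1:1 against a Schroth-only arm with blinded assessors, the sample size is an EG-CG calculation, the Discussion names the additive effect, and section 2.5.2 lists the two-sample test first. The Introduction can also be read as describing data sources: volunteers are measured once and patients twice, and a between-arm comparison of change also uses baseline and post-treatment data. The choice of test for each contrast may be settled in an analysis plan that is not shown.

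Much of this stands. A reader might infer that efficacy will be judged by paired tests alone, or that the plan has no valid test. The documents do not support either reading. An unadjusted two-sample t-test is valid in this design, and planning paired tests alongside it is not in itself an error.

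A reader might also infer a rule of declaring benefit when EG is significant and CG is not. The protocol states no such rule. With equal true change, that pattern has probability p(1 − p), where p is the paired-test power: 0.48 × 0.52 = 0.25 at d = 0.4, but 0.97 × 0.03 = 0.03 at d = 0.8. The 25% is the ceiling of the formula under one assumed change and is not an error rate of this plan.

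What remains is the conflict in the text. An unseen analysis plan could assign the tests, but the aim in the Introduction would still disagree with section 2.2.6 and the Discussion.

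**Conclusion.** The point holds as an inconsistency and an open choice. The efficacy aim describes a before-after comparison and section 2.5.2 leaves the deciding test open, while the objective and the sample size require EG versus CG. The valid test is in the plan but is not designated.

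The size of the problem depends on how the aim is carried out. If a paired test in EG were taken as the evidence, it would be significant in 30% to 97% of trials with no added effect, for common standardised changes of 0.3 to 0.8 at 25 per arm. Those changes are assumptions chosen for illustration, and the figures describe that test and not the plan as a whole. If the between-arm test decides, the 5% level is kept.

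**What to change.** - Introduction: word the efficacy aim as the comparison of EG with CG.
- Section 2.5.2: state that efficacy conclusions rest on the between-arm difference in post-treatment value, adjusted for baseline by ANCOVA, with its 95% CI. Cobb angle is primary, and the secondary measures are treated the same way.
- Section 2.5.2: state that within-arm changes are reported descriptively and are not evidence of efficacy.

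The cost is a few sentences. Baseline values are already collected for every patient, N stays at 30 per group, and the only tests demoted are those that do not address the added effect of manual therapy. The adjustment is a gain in precision, not a condition for validity. The essential change is to designate the between-arm contrast.

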## Materials and methods

2

### Study design and settings

2.1

This study is a prospective randomized controlled trial. This study compares the biomechanical patterns between AIS patients and healthy individuals during standing and walking using technologies such as plantar pressure measurements, 3D gait analysis, sEMG, and IRT, and observes changes in patients before and after treatment. The research will be conducted at the Rehabilitation Medicine Department of the Second Affiliated Hospital of Tianjin University of Traditional Chinese Medicine. A total of 60 patients will be enrolled, along with 15 healthy individuals of similar age. Patients in the control group (CG) will perform the Schroth method for 60 min, five times per week. The experimental group (EG) will receive 20-min TCMMT three times per week in addition to the Schroth method. The total treatment duration for both groups is 8 weeks. The healthy control (HC) will receive no intervention. All patients will be assessed for Cobb angle, 3D gait parameters, sEMG and IRT before and after treatment. The healthy individuals will receive all assessments except the Cobb angle measurement only upon enrollment. The SPIRIT schedule of participant timeline is shown in Figure 1 and the flow chart of the trial procedure is presented in Figure 2.

**Figure 1 fig1:**
[figure not shown]
The SPIRIT schedule of participant timeline.

**Figure 2 fig2:**
[figure not shown]
The flow chart of the trial procedure.

### Study participants

2.2

#### Recruitment strategy

2.2.1

We will screen and recruit participants from December 2025 to August 2026 at the second affiliated hospital of Tianjin University of Traditional Chinese Medicine. Our researchers will be systematically trained and fully informed of the trial procedures. Informed consent will be obtained from participants before enrollment. Participation will be entirely voluntary, and participants will have the right to withdraw from the trial at any time without penalty.

#### Inclusion criteria

2.2.2

Diagnostic criteria for idiopathic scoliosis (1).Ages 8 to 15 years, skeletal immaturity (defined as a Risser grade ≤2) (29, 30).Major curve Cobb angle 10° ~ 40°.No obvious deformities in the lower limbs and feet.Can understand and follow instructions to walk independently.Can understand and voluntarily participate in, and sign the informed consent form.

#### Inclusion criteria for the HC

2.2.3

Ages 8 to 15 years.Can understand and voluntarily participate in, and sign the informed consent form.

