### Outcomes measures

2.4

Collect general information of participants, including name, gender distribution, age, risser grade distribution, height, weight, and medical history.

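### The AIS versus healthy-control comparison may be confounded: the controls are called age-matched but need only fall in the same 8-15 age range, and the named tests are unadjusted

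*Protocol article*

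**What the plan says.** The healthy group is described in three ways. The Abstract says "fifteen age-matched healthy volunteers will be included". Section 2.1 says "along with 15 healthy individuals of similar age". Section 2.2.6 says "we will recruit 15 healthy individuals of the same age". The criteria that define the group, in section 2.2.3, are "Ages 8 to 15 years.Can understand and voluntarily participate in, and sign the informed consent form".

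Patients face more conditions in section 2.2.2, among them "Ages 8 to 15 years, skeletal immaturity (defined as a Risser grade ≤2" and "No obvious deformities in the lower limbs and feet". They must also be able to walk independently on instruction.

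On assessment, section 2.1 says "The healthy individuals will receive all assessments except the Cobb angle measurement only upon enrollment". Section 2.4 collects general information on participants, "including name, gender distribution, age, risser grade distribution, height, weight, and medical history".

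The exclusion list (2.2.4) follows both inclusion lists and carries no group label. It excludes growth, neurological, muscular and skeletal abnormalities. Two of its five items speak of the patient.

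Section 2.5.2 names two-sample or paired t-tests for outcomes, with non-parametric tests if normality fails. It names no covariates.

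**The concern.** The baseline comparison with healthy children is the first aim listed in the Abstract, and the Introduction and section 2.2.6 repeat it. It is not randomised, so only selection or adjustment can make the groups comparable. As written, selection secures a shared age range that spans puberty, and the named tests adjust for nothing.

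The eligibility rules differ on matters close to what is measured. Plantar pressure and gait are compared, but only patients must be free of obvious foot and lower-limb deformity. Only patients must be skeletally immature, so controls may on average be older or more mature. At stake is whether a difference in gait, pressure, muscle activity or skin temperature can be attributed to AIS.

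**Working it through.** **1. The plan's own figure.** Section 2.2.6 gives 30 patients per randomised group.
- Inputs: 10.87 (SD 3.60) and 14.97 (SD 5.01), two-sided alpha 0.05, power 0.90, 15% attrition.
- Difference = 14.97 − 10.87 = 4.10. Pooled SD = √[(3.60² + 5.01²)/2] = 4.36.
- The t-based size is 25 per group, and 25/0.85 = 29.4, so 30. The figure reproduces and does not involve the controls.
- No derivation is given for 15 controls. For 60 v 15, the SE of a difference in SD units is √(1/60 + 1/15) = 0.289. The detectable difference is 0.82 SD at 80% power and 0.95 SD at 90%.

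**2. Criteria side by side.**

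| Item | Patients | Controls |
|---|---|---|
| Age 8-15 | required | required |
| Risser limit | required | not stated |
| Limb and foot criterion | required | not stated |
| Spine assessment | Cobb angle | none stated |
| Exclusion list 2.2.4 | applies | unclear |
| Matching on age, sex or maturity | – | no procedure stated |

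**3. Illustration of confounding by age.** The inputs are assumptions: age uniform over 8-15, so age SD = 7/√12 = 2.02 years; no true AIS effect; a systematic mean age gap g; age-outcome correlation r. Bias in SD units = r × g / 2.02. The rejection rate comes from the noncentral t distribution with noncentrality bias/0.289. For g = 1 and r = 0.5, bias = 0.25 and the rejection rate is 13.5%.

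| Age gap | r = 0.3 | r = 0.5 | r = 0.7 |
|---|---|---|---|
| 0.5 year | 6% | 7% | 9% |
| 1 year | 8% | 14% | 22% |
| 2 years | 17% | 39% | 66% |

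If both groups were random draws from that range, the SE of the mean age difference would be 2.02 × 0.289 = 0.58 years. A 1-year gap is then 1/0.58 = 1.7 SEs and could occur by chance. A purely chance gap is already covered by the nominal 5% on average, so the table concerns gaps produced by how the controls are selected.

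**4. Unrecognised scoliosis among controls.** The Introduction gives an incidence of about 2 to 4%. Reading this as prevalence and assuming no screening:
- At least one affected of 15: 1 − 0.98¹⁵ = 26%; 1 − 0.96¹⁵ = 46%.
- Expected number affected: 15 × 0.02 = 0.3; 15 × 0.04 = 0.6.
- The average AIS-control difference shrinks by only about 2-4%.

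**5. Unequal variances.** This applies only if the pooled t-test is used (critical value 1.993 on 73 df). Take AIS SD = 1; the control SDs below are assumed.
- Control SD 0.5: pooled variance (59 + 14 × 0.25)/73 = 0.856, so assumed variance 0.856 × (1/60 + 1/15) = 0.0713. True variance 1/60 + 0.25/15 = 0.0333. The effective threshold is 1.993/√(0.0333/0.0713) = 2.92, a type I error near 0.4%. Simulation (40,000 runs) gave 0.5%.
- Control SD 1.5: pooled variance (59 + 14 × 2.25)/73 = 1.240, assumed variance 0.1033, true variance 0.1667. The threshold is 1.993/√(0.1667/0.1033) = 1.57, an error near 12%. Simulation gave 12%.
- Welch's test stays near 5% in both cases.

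**The case against.** The exclusion list has no group label and comes after both inclusion lists. If it covers controls, overt skeletal, muscular and developmental abnormality is already excluded, and section 2.6 says participants are enrolled strictly by the criteria. A reader might infer that controls face no health criterion at all; the text does not support that. What remains is unclear scope. The list's explicit scoliosis items (a curve above 40° and non-specific scoliosis) would not plainly remove a child with a mild idiopathic curve. Medical history is collected, but the Introduction itself says AIS is usually without symptoms and easily missed.

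The three descriptions of the controls' age do show intent, and an article may leave a matching procedure to the full protocol. But the article prints a separate list of criteria for controls, and that list sets only the shared range. Sex balance is mentioned nowhere.

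Section 2.5.2 ties no test to this comparison, does not specify the pooled form and allows non-parametric tests. An analysis plan that is not shown may add covariates. The inference that a pooled t-test is planned therefore fails, and the 0.5% and 12% figures cannot carry the point. Every test that is named is nevertheless unadjusted, for a comparison without randomisation.

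The Discussion calls the additive effect of manual therapy the primary objective, and controls have no Cobb measurement. That limits the importance of the point but does not remove it.

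**Conclusion.** The point holds as a risk: the AIS versus control comparison may be confounded by age, sex, maturity or foot differences, and neither the stated criteria nor the named tests guard against this. Saying that it is confounded would go too far, because the protocol gives no age, sex or size gap. Under the assumptions shown, the false-positive rate could stay near 6% or rise well beyond 20%, depending on the gap and on how strongly the outcome follows age.

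Two supporting figures deserve little weight. The 26-46% chance of at least one affected control assumes no screening and reads an incidence as a prevalence, and the dilution it implies is small. The type I error figures hold only for a pooled test with SDs that differ by the assumed ratios.

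A reader might also infer that the trial's main result is at risk. It is not: the randomised comparison and its sample size do not use the controls. The change is worth making because the comparison is a stated aim and the remedy is cheap.

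**What to change.** 1. State that the exclusion list in 2.2.4 applies to controls. Add to 2.2.3 the lower-limb and foot criterion and the absence of known or visible scoliosis, judged by history and inspection at enrolment, without a radiograph.
2. Recruit the 15 controls frequency-matched to the patients on sex and age band, or drop the term age-matched and use one description throughout.
3. Compare patients with controls in a linear model adjusted for age and sex, both already collected. Add height and weight only as a sensitivity analysis, because the curve itself can reduce standing height and adjusting for it may remove part of the AIS effect.
4. With 60 v 15, use the small-sample robust standard error known as HC3 (unrelated to the protocol's abbreviation HC), or Welch's test if unadjusted. The plain robust form, HC0, is not enough: in a simulation with assumed covariates its type I error was 5.5-7.3%, against 4.1-5.0% for HC3.

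The cost is wording, slightly slower recruitment of controls and a little more analysis. No extra patients are needed.
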